### Ethical aspects

See Benefit/risk assessment for a detailed discussion of possible benefits and risks to the patient.

The pilot study will be performed according to the approved protocol, applicable laws and regulations and the ICH Good Clinical Practice (GCP) guideline.

Participation in the trial will be subject to written informed consent, and all participants will be informed of their right to withdraw their consent at any time.

A panel of user representatives have been consulted before and during the development of this study protocol. They have assessed and contributed to the study protocol and all written information given to the participants.

Sponsor will take out a drug liability insurance (LAF) to cover all participants.

Participants will not be charged for assessments or treatments under the study protocol. No financial compensation will be offered.

Source data including medical journals will be made available for monitoring and in the event of an inspection/audit from NOMA.

### Financial support

Daratumumab is under patent for Janssen pharmaceutical company until 2025/26. The drug costs are considerable, but with the backing of ME/CFS support groups, we have funding for this pilot study for six patients, including lab and biobank investigations.

The ME/CFS research group at Haukeland University Hospital receives funding from the Kavli Trust. This pilot study will be performed with financial support from the patient organizations the Norwegian ME association, MENiN, MEandYou and Fokus på ME. The funding organizations have had no role in the study design.

## Publication

The pilot study will be published in a peer-reviewed journal, regardless of the outcome of the trial.

## Appendix 1: Safety

### Safety monitoring

Safety assessment will consist of monitoring and recording all AEs by the principal investigator, including Serious Adverse Events (SAE), besides regular monitoring of hematological status. Any clinically significant change in a laboratory parameter will be defined as AE.

### Adverse event/ serious adverse event

#### Definition of adverse events (AE)

An Adverse Event (AE) is any untoward medical occurrence in a patient administered a pharmaceutical product and which does not necessarily have to have a causal relationship with this treatment. It can therefore be any unfavorable and unintended sign, symptom, or disease temporally associated with the use of a medicinal product, whether or not considered related to the medicinal product. This includes any occurrence that is new in onset or aggravated in severity from the baseline condition, or abnormal results of any diagnostic procedures, including laboratory testing abnormalities.

All toxicity will be graded according to Common Terminology Criteria for Adverse Events (CTCAE) guidelines (version 5.0).

Adverse events will be graded using the following criteria:

- Grade 1 (Mild): discomfort noticed but no disruption of normal daily activity.
- Grade 2 (Moderate): discomfort sufficient to reduce or affect normal daily activity.
- Grade 3 (Severe): inability to work or perform normal daily activity.
- Grade 4 (Life-threatening or disabling): represents an immediate threat to life.

Furthermore, adverse events will be classified into serious adverse event (SAE) yes/no.

#### Definition and reporting of serious adverse events (SAE)

SAE is any clinical AE or abnormal laboratory test value that is serious and occurring during the course of the study, irrespective of the treatment received by the patient.

A SAE is any experience that suggests a significant hazard, contraindication, side effect or precaution. This includes any experience which:

- is fatal (note that death is an outcome, not an event).
- is life-threatening.
- requires in-patient hospitalization or prolongation of existing hospitalization.
- results in persistent or significant disability/incapacity.
- is a congenital anomaly/ birth defect.
- is medically significant or requires intervention to prevent one or more outcomes

listed below.

For reports of hospitalization, it is the sign, symptom, or diagnosis which led to hospitalization that is the serious event for which details must be provided. Any event requiring hospitalization or prolongation of hospitalization that occurs during the study must be reported as a SAE, except hospitalization of the following:

- hospitalization not intended to treat an acute illness or adverse event (e.g., social reasons, administration of study drug or study procedures).
- surgery or procedure planned before entry into the study (Note: hospitalization that were planned before the signing of consent form and where the underlying condition for which the hospitalization was planned has not worsened, will not be considered SAE. Any AE that results in a prolongation of the originally planned hospitalization is to be reported as a new SAE.

SAE must be reported to the sponsor within 24 hours of investigator/study nurse detecting the event or learning about it. Reporting is done through eCRF and by direct contact (by mail or telephone) to sponsor.

#### Suspected Unexpected Serious Adverse Reactions (SUSAR)

All **suspected** Adverse Reactions which occur in the trial and that are both **unexpected** and **serious**. Suspected adverse reactions (AR) are those AEs of which a reasonable causal relationship to any dose administered of the investigational medicinal product and the event is suspected. Unexpected adverse reactions are adverse reactions, of which the nature, or severity, is not consistent with the applicable product information (e.g. Investigator's Brochure for an unapproved IMP or Summary of Product Characteristics (SPC) for an authorized medicinal product).

Such an event must be reported to the sponsor within 24 hours of investigator or study nurse detecting the event or learning about it. Reporting is done through the eCRF and by direct contact (by mail or telephone) to sponsor. SUSARS will be collected and reported to the competent authorities and ethics committees. If an SAE is deemed a SUSAR, reporting to NOMA will take place within 7 days (fatal or life-threatening SUSAR) or 15 days (other SUSARs) from receipt of notification of the event. A final report of SAEs will be submitted to the Norwegian Medicines Agency (NOMA) at the end of study.

#### Documenting assessment and reporting of adverse events

The investigator is responsible for ensuring that all AEs (including SAEs) that are observed or reported during the study, as outlined in the prior sections, are recorded on the eCRF. Adverse

events will be scored according to the NCI Common Terminology Criteria for Adverse Events, version 5.0 (See appendix VI). Investigator will assess the occurrence of AEs and SAEs at all subject evaluation time points during the study. All AEs and SAEs, whether volunteered by the subject, discovered by study staff during questioning, or detected through physical examination, laboratory testing, or other means, will be recorded in the subject's medical record and on the AE eCRF.

Each recorded AE or SAE will be described by its duration, severity, suspected relationship to the investigational product, and any action taken.

Adverse events will be reported from the time of signature of informed consent until the end of study for the patient.

If an AE or SAE is present at the withdrawal visit or at the subject's last participation in the study, it should be followed until the time of resolution or stabilized unless the subjects is lost to follow up. Resolution means the subject has returned to baseline state of health or the investigator does not expect any further improvement or worsening of the event.

Adverse events occurring after the end of follow-up in the study should also be reported if considered at least possibly related to the investigational medicinal product by the investigator.

Pre-existing conditions will be collected on the baseline concomitant diseases CRF, i.e., active (symptomatic) diseases of CTCAE grade 2, diseases under treatment, chronic diseases and long-term effects of past events as present at the time of baseline assessment.

All adverse events have to be reported with **the exception of:**

1. A pre-existing condition that does not increase in severity; the pre-existing condition should be reported on the baseline concomitant diseases CRF.
2. Any grade 1 adverse event.

### Causality assessment of Serious Adverse Event

The investigator will decide whether the serious adverse events is related to the investigational treatment, i.e. daratumumab. The decision will be recorded on the serious adverse event report. The assessment of causality is made by the investigator using the following:

| RELATIONSHIP   | DESCRIPTION                                                                                                                                                                                                                                                                                                              |
|----------------|--------------------------------------------------------------------------------------------------------------------------------------------------------------------------------------------------------------------------------------------------------------------------------------------------------------------------|
| UNRELATED      | There is no evidence of any causal relationship                                                                                                                                                                                                                                                                          |
| UNLIKELY       | There is little evidence to suggest there is a causal relationship (e.g., the event did not occur within a reasonable time after administration of the trial medication).

There is another reasonable explanation for the event (e.g., the patient's clinical condition, other concomitant treatments).           |
| POSSIBLE       | There is some evidence to suggest a causal relationship (e.g., because the event occurs within a reasonable time after administration of the trial medication).

However, the influence of other factors may have contributed to the event (e.g., the patient's clinical condition, other concomitant treatments). |
| PROBABLE       | There is evidence to suggest a causal relationship and the influence of other factors is unlikely.                                                                                                                                                                                                                       |
| DEFINITELY     | There is clear evidence to suggest a causal relationship and other possible contributing factors can be ruled out.                                                                                                                                                                                                       |
| NOT ASSESSABLE | There is insufficient or incomplete evidence to make a clinical judgment of the causal relationship.                                                                                                                                                                                                                     |

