### Daratumumab intervention

After 12 weeks’ run-in, patients will start intervention.

The first two patients will receive two subcutaneous injections of daratumumab two weeks apart, followed by an observation period of four to six weeks. If there is no serious, unexpected toxicity, we will proceed with another two injections two weeks apart.

After these two patients have received the planned four daratumumab subcutaneous injections, the Safety board will review the data.

Subject to a favorable Safety board review, the pilot study will proceed with the four remaining patients, who will receive four subcutaneous injections of daratumumab two weeks apart.

Thus, all patients will receive in total four subcutaneous injections of daratumumab.

According to a second amendment to the protocol, among four additional patients included, provided clinical improvement at week 24, these will receive additional three daratumumab injections, at weeks 26, 34 and 42, and with extended follow-up until week 72.

The injections will be administered in the outpatient clinic in the Department of Oncology and Medical Physics at Haukeland University Hospital.

Oral premedication will be given at least one hour before daratumumab injection. Before the first daratumumab injection: Dexamethasone 10 mg orally, Cetirizine 10 mg orally, Paracetamol 1 g orally, Montelukast 10 mg orally. Also, at least 20 minutes before daratumumab: Dexchlorpheniramine 5 mg iv.

On the following two days (2 and 3): Dexamethasone 4 mg orally.

Before the second and subsequent daratumumab injections, if no reaction to the first injection: Dexamethasone 10 mg orally, Cetirizine 10 mg orally, Paracetamol 1 g orally.

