## Adverse events and Safety board

### Adverse events

Investigators will assess and classify adverse events (AE), serious adverse events (SAE), and SUSAR (suspected unexpected serious adverse reactions) according to the Common terminology criteria for adverse events (CTCAE), version 5.0 and the study drug SmPC.

For the purpose of safety and toxicity assessment, adverse events from grade 2 (moderate) and upwards, with possible, probable or certain causal relationship with the study drug will be reported. All SAE will be reported, regardless of causality.

Elective or pre-planned hospital admissions arranged prior to the start of study, or planned hospital admissions for trial specific procedures or treatment are not considered SAE.

Definitions and procedures for assessments and reporting of adverse events are described in appendix 1.

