### Possible risks

The participants may experience side effects from the intervention. We cannot be certain that the anti-CD38 antibody treatment will be associated with a beneficial disease course, and patients could in theory also experience worsening of their ME/CFS symptoms.

A lack of clinical response may represent a psychological burden to the patients.

For patients with moderate (mainly house-bound) or severe (mainly bedridden) ME/CFS, participating in a clinical trial may cause temporary worsening due to the stress involved in performing study-specific procedures, such as travelling to the hospital, taking blood samples, receiving subcutaneous interventions and completing questionnaires.

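### Relatedness is judged against daratumumab alone, and the main-text reporting filter can then drop non-serious events ascribed to premedication, travel or study procedures, contrary to the protocol's own all-cause rules

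*Protocol*

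**What the plan says.** **Reference for causality.** Appendix 1, Documenting assessment and reporting of adverse events, requires each recorded event to be described by, among other things, its "suspected relationship to the investigational product, and any action taken". The causality section of Appendix 1 names daratumumab as the reference for serious events: "The investigator will decide whether the serious adverse events is related to the investigational treatment, i.e. daratumumab". Neither section provides for attribution to premedication or to study procedures.

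**What is reported.** The main-text section Adverse events restricts the safety and toxicity assessment to events of grade 2 and above "with possible, probable or certain causal relationship with the study drug will be reported". The same section reports all serious events irrespective of causality.

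**What else accompanies the injection.** Under Daratumumab intervention: "Oral premedication will be given at least one hour before daratumumab injection". More drugs are added at the first injection. Under Possible risks, for housebound or bedridden patients: "participating in a clinical trial may cause temporary worsening due to the stress involved in performing study-specific procedures". Travel to hospital is among the examples given there.

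**The other rules.** Endpoints and statistical analyses defines the primary outcome through treatment-emergent adverse events, with no relatedness condition. Data registration and management puts every event of grade 2 or higher in the CRF. Appendix 1 records all events on the eCRF. It requires all to be reported except grade 1 events and pre-existing conditions that have not worsened.

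**The concern.** The main purpose of the pilot is feasibility and safety of the injections in moderately to severely ill patients. In this protocol the injection always comes with premedication and a hospital attendance, so a later trial would meet the tolerability of that whole package. The protocol itself names two possible sources of worsening: the drug, and the effort of taking part. It gives the investigator one relatedness question to cover both.

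If the main-text filter decides what is reported, the toxicity summary depends on a judgement about daratumumab alone. An event put down to another protocol-imposed component can then leave the report of the primary outcome. With ten patients, each such event matters. An analysis plan cannot repair this later, because it cannot recover an attribution that was never collected.

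**Working it through.** No sample size, power or event rate enters, so the check is a comparison of rules, followed by a count of exposure.

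**Step 1: which relatedness categories pass the filter.** The Appendix 1 scale has six categories: unrelated, unlikely, possible, probable, definitely, not assessable. The main text reports three: possible, probable and certain (taking certain to mean definitely). The other three are not reported if the event is non-serious. The scale stands under a heading on serious events. I assume the same terms are meant for non-serious events, since the main text uses them there.

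**Step 2: follow one event through each rule.** Take an event that the investigator ascribes to premedication or travel and does not consider at least possibly related to daratumumab.

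| Event | Adverse events (main text) | Data registration and management | Appendix 1, Documenting | Primary outcome |
|---|---|---|---|---|
| Non-serious, grade 2+ | Not reported | Registered in CRF | Recorded and reported | Counts if treatment-emergent |
| Serious | Reported | Registered if grade 2+ | Recorded and reported | Counts if treatment-emergent |
| Grade 1, non-serious | Not reported | Not required | Recorded, not reported | No grade limit stated |

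The rules disagree on causality in the first row, and that is the row at issue. Post-visit worsening of ME/CFS is not removed by the Appendix 1 exception, which covers only pre-existing conditions that do not increase in severity.

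**Step 3: is the score itself fixed?** No. The *unlikely* row reads "There is another reasonable explanation for the event (e.g., the patient's clinical condition, other concomitant treatments", which fits an event firmly put down to premedication. The *possible* row, however, also allows for concomitant treatments as a contributing factor, and it is triggered by timing after the trial medication. Premedication and injection fall on the same day, so *possible* is open too.
- Scored *unlikely*, *unrelated* or *not assessable*: a non-serious event is left out by the main-text filter.
- Scored *possible*: it is reported, but only as related to daratumumab, and the suspected source is not captured.

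Neither route records what the investigator actually suspected.

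**Step 4: exposure.**
- Injections: six patients × 4 = 24. The four added patients have up to 4 + 3 = 7 each, so 4 × 7 = 28. Maximum 24 + 28 = 52. If none of the four continues, 10 × 4 = 40.
- Attendances without maintenance: weeks 0, 12, 14, 16, 18, 20, 32, 52 = 8 per patient. With maintenance: weeks 0, 12, 14, 16, 18, 20, 26, 34, 42, 52 = 10 per patient. Range: 10 × 8 = 80 to 6 × 8 + 4 × 10 = 88.

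These are occasions on which such an event could arise. No rate is given, so no number of dropped events follows from them.

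**The case against.** The strongest reply is that nothing is lost. Appendix 1 and Data registration and management capture every grade 2+ event whatever its cause, an adverse event is defined irrespective of causality, and the primary outcome has no relatedness condition. The main-text filter might then be read as governing only a summary of suspected drug toxicity. This stands in part: the events should be in the database, and it would be wrong to say that they all disappear. But the main text introduces its filter for the safety and toxicity assessment as a whole, not for a supplementary table. A reader following that section would leave the events out.

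Second, judging causality against the investigational product is normal and matches the SUSAR definition. That is correct, and it is a reason to keep that basis for SUSARs. It is not a reason to let the same judgement decide what counts as tolerability.

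Third, worsening is also followed through SF-36, DSQ-SF, function level and step counts, including during the drug-free run-in. That helps for worsening of ME/CFS. It does not cover reactions to premedication, and these measures belong to the secondary objectives.

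A reader might also infer that such events must be scored *unlikely*, or that the protocol lists premedication among its risks. The text supports neither. The scale leaves *possible* open. Only participation and procedures appear under Possible risks, while premedication appears under Efforts to reduce risks as a protective measure. Nor does the sentence naming daratumumab as the reference for serious events cause any loss, because all serious events are reported. The weight rests on the main-text filter and on the relationship field that Appendix 1 asks for with every event.

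**Conclusion.** The point holds in this form. Causality has one reference, daratumumab, and the main-text filter can remove non-serious grade 2+ events ascribed to premedication, travel or study procedures from the reported toxicity. That filter contradicts the unrestricted primary outcome, the CRF rule and the all-cause rule in Appendix 1, and these sections must be reconciled. Even if every event is reported, its suspected relation to premedication or procedures has no field of its own.

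The size cannot be put as a number of events. It lies between none, if Appendix 1 is followed, and all non-serious grade 2+ events not judged at least possibly related to daratumumab, if the main text is followed. The 40 to 52 injections and 80 to 88 attendances measure exposure only. The conclusion assumes that the Appendix 1 terms apply to non-serious events and that the main-text filter governs what is presented. It is worth correcting because it affects how the primary outcome is reported, and the correction is cheap.

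**What to change.** 1. In the main-text section Adverse events, replace the relatedness filter with a statement that all adverse events of grade 2 or higher are reported regardless of causality. This aligns it with the primary outcome, with Data registration and management and with Appendix 1. Drug-related events can still be shown as a subset.
2. In Appendix 1 and on the AE form, record three separate judgements for each event: suspected relation to daratumumab, to protocol premedication, and to study procedures or travel.
3. State that relation to daratumumab alone remains the basis for SUSAR reporting.

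The cost is two extra fields, a few sentences of amendment and a somewhat higher reported event count. For patients already treated, the two new judgements would have to be completed from the medical record and marked as retrospective. No dose, schedule or clinical rule changes.
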